### Concomitant medication

Study participants will have any heart rate-limiting drugs cautiously withdrawn prior to commencing the 6-week trial protocol. These include beta-blockers, rate-limiting calcium antagonists (e.g., diltiazem and verapamil), and ivabradine to ensure a normal chronotropic response to exercise stress testing. Long-acting oral nitrates and nicorandil will also be stopped to avoid any potential interference with haemodynamic physiology. Patients will be allowed to continue their antiplatelet therapy (e.g., aspirin, clopidogrel, prasugrel, and/or ticagrelor), ACE-inhibitors, angiotensin receptor blockers, and statins. Patients will also continue their sublingual glyceryl trinitrate (GTN) spray or buccal GTN to relieve breakthrough angina. Those patients experiencing poor control of pre-existing hypertension following the cessation of the drugs listed previously will be prescribed alternative antihypertensive medication at the discretion of the investigator, or have their current medication they can continue up-titrated, and monitored closely for response.

## Study visits and procedures

### Screening Visit

Once a patient is deemed to have adequately fulfilled the inclusion and exclusion criteria, informed consent will be obtained. Part of the inclusion criteria includes the demonstration of reversible ischaemia during an ETT. If a recent ETT is not available, the patient will be asked to perform an ETT (free of any heart rate-limiting medication for the past 48 hours) at the screening visit. The result of this ETT will not be used in the final data analysis but will be captured as part of the screening process. Those patients ineligible for trial participation will be registered, and the reason for screening failure will be recorded. Patients entering the trial will receive a tutorial on home blood glucose monitoring and the signs and symptoms of hypoglycaemia. A safety information card will be issued. A full medical history and clinical examination will be performed. Blood tests will be taken (Table 6). Medications that need to be withheld will be identified at this visit and withdrawn cautiously (see Table 7). Those patients successfully recruited will be randomised at this stage.

**Table 6 Tab6:** **Laboratory tests**

**The following blood tests will be taken at each study visit (Table** **7** **) unless otherwise stated:**	
•	Full blood count
•	Creatinine and electrolytes
•	Estimated glomerular filtration rate
•	Liver function tests
•	Amylase
•	Corrected calcium
•	Random blood glucose
•	HBA_1c_ (Week 3 and Week 6 only)
•	Random lipid profile (serum total cholesterol, low-density lipoprotein cholesterol, high-density lipoprotein cholesterol, and triglyceride) (Week 3 and Week 6 only)

**Table 7 Tab7:** **LIONESS trial flowchart of visits and procedures**

	**Screening visit**	**Commence trial (Week 0)**	**Study visit (Week 1)**	**Exercise test 1 (Week 2)**	**Exercise test 2 (Week 3)**	**Study visit (Week 4)**	**Exercise test 3 (Week 5)**	**Exercise test 4 (Week 6)**
Obtain informed consent, issue safety information card and patient diary	Yes	-	-	-	-	-	-	-
Randomisation to study agents	Yes	Perform first self-administration of study agent	-	-	-	-	-	-
Issue 7-day course of blinded study agent	-	Yes	Yes	Yes	Yes	Yes	Yes	Stop all study medication
Check study drug compliance	-	-	Yes	Yes	Yes	Yes	Yes	Yes
Withdraw protocol-mandated pre-existing patient medication	Tutorial and commence withdrawal	Complete withdrawal	-	-	-	-	-	Recommence pre-existing patient medication
Home Blood Glucose Monitoring	Tutorial and issue equipment	-	Record data from patient diary	Record data from patient diary	Record data from patient diary	Record data from patient diary	Record data from patient diary	Record data from patient diary
Physical examination	Yes	Yes	Yes	Yes	Yes	Yes	Yes	Yes
Height measurement	Yes	-	-	-	-	-	-	-
Weight measurement	Yes	Yes	Yes	Yes	Yes	Yes	Yes	Yes
Blood pressure measurement	Yes	Yes	Yes	Yes	Yes	Yes	Yes	Yes
Electrocardiogram	Yes	-	-	-	-	-	-	-
Pre-specified blood tests	Yes	Yes	Yes	Yes	Yes	Yes	Yes	Yes
Perform supervised exercise tolerance test (ETT)	Yes (if recent ETT unavailable)	-	-	Yes	Yes	-	Yes	Yes

### Trial visits (week 0 to week 6)

Trial participants will perform their first self-administration of study agent and first blood glucose measurement, which will be recorded in their patient diary, at trial commencement (Week 0). Both will be supervised by an investigator. Recruited patients will attend a total of 7 study visits and have procedures performed according to the schedule detailed in Table 7. Patients will be asked to record twice daily home blood glucose measurements at approximately the same time am and pm. Patients will have blood tests performed at every study visit (Table 6).

### Expected duration of the study

From the point of administration of study drug on day 1 the total length of the study will be 6 weeks. There will be no follow-up of patients after completion of the 6-week trial protocol, at which point study drugs will be terminated and patients will have their pre-study medication recommenced immediately thereafter.

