### Sample size calculation

The host department has shown that the time taken to 0.1 mV STD (368 ± 34 → 418 ± 36 seconds) and the rate pressure product at 0.1 mV STD (20500 ± 755 → 21907 ± 764 mmHg/min) is significantly increased during the second of two serial exercise tests separated by 15 minutes in chronic CAD patients with known left anterior descending artery stenoses [47,48]. This effect is attributed to warm-up angina, which is thought to augment the innate resistance of the myocardium to an ischaemic insult [51,52]. We would expect the administration of Liraglutide to mimic the beneficial cardioprotective effects of warm-up angina. A sample size of 26 patients randomised in a 1:1 fashion to each treatment arm (taking into consideration a >10% drop-out rate) followed by crossover would have 90% power to detect a difference between the means of approximately 15% (2-sided α = 0.05).

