### Procedures for recording and reporting adverse events

All study participants will be issued a patient diary in which they can record any adverse events, side effects, injection site reactions and angina burden. This diary will be inspected at every study visit. Patients will also be able to contact the Main Patient Liaison at all times for general enquiries and advice regarding any signs and symptoms they are experiencing pertaining to the study. The primary care physicians of all study participants will be issued with an information sheet regarding the potential side effects of the GLP-1R agonist Liraglutide and the medication that a patient may have had discontinued prior to commencing the trial. The importance of informing the Main Patient Liaison if any adverse events were to occur will be stressed.

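### No contact is scheduled after Week 6, when placebo-first patients have just finished 1.8 mg liraglutide and completers who had cardiac drugs withheld restart them; one telephone call would add planned event capture

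*Protocol article*

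**What the plan says.** The section Expected duration of the study fixes the end of observation: "There will be no follow-up of patients after completion of the 6-week trial protocol". It stops study drug at that point and has pre-study medication restarted straight away. Table 7 agrees. Its last column is Week 6, with the entries "Stop all study medication" and "Recommence pre-existing patient medication".

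Under Study design, the active period runs one week each at 0.6, 1.2 and 1.8 mg, with crossover at Week 3. Placebo-first patients are therefore on 1.8 mg in the week before the Week 6 visit.

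Under Concomitant medication, patients have "any heart rate-limiting drugs cautiously withdrawn prior to commencing the 6-week trial protocol", and long-acting nitrates and nicorandil are also stopped. If blood pressure control then worsens, patients receive an alternative antihypertensive "or have their current medication they can continue up-titrated, and monitored closely for response".

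Adverse events are recorded in a patient diary: "This diary will be inspected at every study visit". There is also a route that the patient can start: "Patients will also be able to contact the Main Patient Liaison at all times". Primary care physicians receive an information sheet and are asked to report events (Procedures for recording and reporting adverse events).

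**The concern.** Two drug changes coincide with the last scheduled contact. Half of the randomised patients come off the top dose of the study drug, and those who gave up cardiac drugs for the trial go back on them.

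An event that starts in the days after the last liraglutide dose will be asked about at a visit if the patient took liraglutide first. If the patient took it second, the event is recorded only if someone volunteers it. Planned ascertainment after the drug therefore depends on sequence.

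The restart is also less closely watched than the withdrawal. Withdrawal runs from screening to Week 0 and is followed by weekly visits. The last scheduled blood pressure, by contrast, is taken before the restart, and no later enquiry is planned. These are angina patients with a coronary stenosis above 70% (Table 4), and the trial itself brings about this medication change.

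**Working it through.** The plan gives no figure to reproduce here. The check is a day count from the schedule and elimination arithmetic from the stated half-life.

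**Inputs**
- Half-life 10-14 h, and five half-lives as the washout mark (Data management and analysis).
- First dose supervised at the Week 0 visit (Trial visits), taken here as day 0.
- Seven syringes per study week (Study agent and placebo comparator), issued at Weeks 0 to 5 and none at Week 6 (Table 7).
- 26 patients randomised 1:1, "taking into consideration a >10% drop-out rate" (Sample size calculation).
- Assumptions: visits exactly 7 days apart, and one dose daily at the visit's time of day.

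**Day of the last liraglutide dose.** There are 6 issues × 7 = 42 syringes, covering days 0 to 41. The first 21 cover days 0 to 20.

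| | Liraglutide first | Placebo first |
|---|---|---|
| Weekly visits during exposure | Weeks 1, 2, 3 | Weeks 4, 5, 6 |
| Last 1.8 mg dose | day 20 | day 41 |
| Visit about 24 h later | Week 3 (day 21) | Week 6 (day 42) |
| Scheduled visits after that | Week 4 (day 28), Week 5 (day 35), Week 6 (day 42) | none |
| First of these after last dose | 28 − 20 = 8 days (192 h) | none |

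The sequences are matched up to and including the visit about 24 h after the last dose. They part only after that.

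**Clearance left at the Week 6 visit, placebo first.** The five-half-life mark is 5 × 10 = 50 h to 5 × 14 = 70 h. Subtracting the 24 h already elapsed leaves 50 − 24 = 26 h to 70 − 24 = 46 h. The fraction remaining at 24 h is 2^(−24/10) = 19% to 2^(−24/14) = 30%.

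**Would a call one week later be late enough?** A call on day 49 falls 49 − 41 = 8 days after the last dose, the same interval as the Week 4 visit in the other sequence. At only 7 days the fraction remaining is at most 2^(−168/14) = 0.02%, so the call looks back over the whole clearance period and the first week on restarted drugs.

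**Patients concerned.** The plan gives only a lower bound on dropout, so the 20% and 30% rates and equal dropout by sequence are assumptions.

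| Dropout | Completers | Placebo-first completers |
|---|---|---|
| 10% | 26 × 0.9 = 23.4 | 11.7 |
| 20% | 26 × 0.8 = 20.8 | 10.4 |
| 30% | 26 × 0.7 = 18.2 | 9.1 |

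The restart applies to completers in both sequences who had a drug withheld: at most about 18-23. The number taking such drugs at entry is not given.

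**The case against.** The strongest case against is that this is an openly stated choice in a small physiological study, with no contradiction and no demonstrated harm. The drug clears within days. Liaison access is continuous, primary care physicians are informed, and the restarted drugs are the patients' own. The Week 4 visit is the first visit of the second period, not a designed post-drug safety check; any two-period crossover that ends at its last assessment has the same asymmetry. Much of this stands. It makes the point minor and confines it to planned capture; access to care is not in question. It does not remove the point, because the article expressly rules follow-up out. This is not detail left to a fuller document.

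A reader might infer more than the documents support:

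- **That safety monitoring of liraglutide is unequal.** Each sequence has three weekly visits during exposure, with the same examination, blood pressure, bloods and diary review. The safety outcomes in Table 3 are covered for every active week in both.
- **That every patient restarts cardiac drugs.** The adverse-event section refers only to medication that a patient may have stopped.
- **That up to 70 h of clearance remain after Week 6.** That needs a dose at the Week 6 visit. With 42 syringes used as scheduled, none is left for day 42.
- **That a call would close the gap entirely.** It cannot measure blood pressure or repeat a blood test.
- **That Week 6 results and diaries are ignored.** A condensed article may leave their handling to the full protocol. Table 7 is also not a complete list of contacts, since Table 3 mentions telephone contact that the flowchart omits.

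**Conclusion.** The point holds as a minor design weakness. After Week 6, placebo-first patients (13 as randomised; about 9-12 completers at 30-10% dropout) have no scheduled contact following their last 1.8 mg dose beyond the visit about 24 h after it, with 26-46 h of clearance to run. Liraglutide-first patients have three later visits. No planned enquiry covers the restart of withheld drugs in either sequence.

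The timing rests on weekly visits, a fixed dosing time and syringes used as issued. The documents give no rate of late events, so no number of missed events can be stated. The exercise tests are complete by Week 6, so the primary endpoints, sample size and power do not change.

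**What to change.** Amend Expected duration of the study and Table 7 to add one telephone adverse-event contact for every patient about one week after the Week 6 visit (day 49). Ask about new events, diary entries since Week 6 and tolerance of any restarted medication, and prompt a clinical check where the answers call for one. Calling everyone, whatever the sequence, keeps the allocation concealed. Telephone contact is already named in Table 3, so the method is not new to the trial.

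The cost is up to 26 calls. At an assumed 10-15 minutes each that is 260-390 minutes, or 4.3-6.5 staff hours, plus one case report form page and an amendment during recruitment. The first patient was recruited in January 2014 and recruitment was still open in February 2015 (Discussion), so patients who have already completed cannot receive a timely call. The report should state how many patients were called.

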### Procedures for recording and reporting adverse events

All study participants will be issued a patient diary in which they can record any adverse events, side effects, injection site reactions and angina burden. This diary will be inspected at every study visit. Patients will also be able to contact the Main Patient Liaison at all times for general enquiries and advice regarding any signs and symptoms they are experiencing pertaining to the study. The primary care physicians of all study participants will be issued with an information sheet regarding the potential side effects of the GLP-1R agonist Liraglutide and the medication that a patient may have had discontinued prior to commencing the trial. The importance of informing the Main Patient Liaison if any adverse events were to occur will be stressed.

### Withdrawal of subjects

Participants will have the right to withdraw from the study at any time for any reason. Should a patient decide to withdraw from the study, all efforts will be made to report the reason for withdrawal as thoroughly as possible. The investigator also has the right to withdraw patients from the study in the event of inter-current illness, adverse events or serious adverse events, protocol violations, administrative reasons or other reasons.

The study drug will be discontinued and the participant withdrawn from the study if:the participant misses 2 consecutive courses of treatment;the participant decides they no longer wish to continue;if the participant experiences an intolerable degree of angina as a result of withdrawing their pre-study heart rate-limiting or anti-anginal medications;if the participant experiences significant side effects from their study medication, in particular excessive or intolerable nausea, vomiting or diarrhoea; orthe investigator recommends it.

The Sponsor or Chief Investigator may prematurely discontinue the study on the basis of new safety information or for other reasons given by the Study Steering Committee or Research Ethics Committee concerned.

### Data management and analysis

Data will be collected prospectively using a customised paper Case Report Form (CRF). Investigators will record adverse events, injection site reactions, angina episodes and clinical and laboratory parameters on the CRF at each study visit.

The fundamental principle underpinning the design of this trial is that the 2-week period between the Week 3 ETT and the Week 5 ETT (see Figure 1), in those patients randomised to the active liraglutide intervention first, should be sufficient to allow adequate washout of the drug and therefore minimise the impact of a potential carryover effect. Given that the half-life of liraglutide is 10–14 hours, this 2-week washout period far exceeds the generally accepted mark of ≥5 half-lives. A washout period for those randomised to the placebo arm first would not apply per se. A preliminary test, such as the Wilcoxon rank sum test, will be applied to ensure there is no carryover effect. Once this has been established, standard two-sample t-tests for independent samples using the intra-individual differences between the outcomes in both study periods as the raw data will be utilised [53].

A multiple regression model will be used to compare treatment, visit number, and patient, using least squares. Linear regression will be used to study the correlation between outcome parameters and baseline patient characteristics. A p value <0.05 will be considered statistically significant.

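### The treatment t-test is made conditional on a preliminary carryover test that, with about 23 completers, cannot show that carryover is absent

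*Protocol article*

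**What the plan says.** All of this stands in the Protocol article, Data management and analysis, unless noted.

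- The section opens with a washout argument for the two weeks between the Week 3 and Week 5 exercise tests: "Given that the half-life of liraglutide is 10–14 hours, this 2-week washout period far exceeds the generally accepted mark of ≥5 half-lives".
- It then adds a test: "A preliminary test, such as the Wilcoxon rank sum test, will be applied to ensure there is no carryover effect". Neither the variable tested nor the test level is given.
- The treatment comparison depends on the outcome of that test: "Once this has been established, standard two-sample t-tests for independent samples using the intra-individual differences between the outcomes in both study periods".
- A further model is named: "A multiple regression model will be used to compare treatment, visit number, and patient, using least squares". It lists no carryover term and is not described as the analysis to use if the preliminary test rejects.
- The general threshold is "A p value <0.05 will be considered statistically significant".
- The Sample size calculation section plans "A sample size of 26 patients randomised in a 1:1 fashion to each treatment arm", "taking into consideration a >10% drop-out rate". It sizes the trial for the treatment difference only and gives no power for the carryover test.

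**The concern.** The section sets a two-stage rule: test for carryover, then test treatment if carryover has been ruled out. A non-significant result is weak evidence of absence unless the test has good power, and here it does not. The usual carryover test in a two-period crossover compares patient totals between the two sequences, so it carries the full between-patient variation that the crossover was chosen to remove.

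Two things are at stake. If carryover exists, a pass would be read as clearance although the treatment estimate is biased. If carryover does not exist, a chance rejection blocks a sound analysis, and this document does not say what is done next. An undefined step at that point invites a choice made after seeing the data.

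**Working it through.** **The plan's own figure.** The claim of 26 patients, 90% power and a difference of about 15% cannot be rebuilt from the article, which gives no SD for the outcome or for within-patient differences. It can be used for calibration. With about 10% drop-out, 26 × 0.9 = 23.4, so about 23 completers, taken as 12 and 11. For 90% power at two-sided 0.05 the noncentral t requires τ/SD_d ≈ 0.709, where τ is the treatment effect and SD_d the SD of within-patient differences. For a 15% effect this means SD_d ≈ 15/0.709 ≈ 21% of baseline. The point does not dispute the sample size.

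**Assumptions not in the document.** One value per patient and period; normal errors with equal variance σ² in both periods; the pre-test is applied to patient totals; within-patient correlation ρ from 0.3 to 0.8.

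**Formulas.** Let λ be the carryover of liraglutide into a following placebo period, and k = √(1/12 + 1/11) = 0.417.

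- Treatment test: SD_d = σ√(2(1−ρ)). The estimate has expectation τ − λ/2 and standard error SD_d × k/2.
- Carryover test: SD_total = σ√(2(1+ρ)) = SD_d × √((1+ρ)/(1−ρ)). The contrast has expectation λ and standard error SD_total × k.

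**Effect of carryover on the treatment test (21 df).**

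- λ = 0: noncentrality 2 × 0.709/0.417 = 3.40, power 90%.
- λ = τ/2: the estimate is 75% of τ, noncentrality 0.75 × 3.40 = 2.55, power 68%.
- λ = τ: the estimate is 50% of τ, noncentrality 0.5 × 3.40 = 1.70, power 37%.

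**Chance of detecting λ = τ.** The noncentrality is 0.709/(0.417 × √((1+ρ)/(1−ρ))). The Wilcoxon columns were simulated with 20,000 runs per setting.

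| ρ | SD_total/SD_d | Noncentrality | t-test on totals, 5% | Wilcoxon, 5% | Wilcoxon, 10% |
|---|---|---|---|---|---|
| 0.3 | 1.36 | 1.25 | 22% | 19% | 30% |
| 0.5 | 1.73 | 0.98 | 16% | 14% | 23% |
| 0.7 | 2.38 | 0.71 | 11% | 9% | 16% |
| 0.8 | 3.00 | 0.57 | 8% | 7% | 14% |

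Separate simulation runs differ by about one point, hence the rounded ranges of 7–20% and 14–31%. For λ = τ/2 the 5% Wilcoxon test rejects about 5–8% of the time, close to its false-alarm rate. A t-test on totals would reach 80% power only for a carryover of 2.3 times τ (ρ = 0.3) to 5.2 times τ (ρ = 0.8).

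**No carryover.** At the 5% level the Wilcoxon test rejects about 4–5% of the time per endpoint. If the treatment test is then dropped, the chance of a significant result is about 0.90 × (1 − 0.044) = 0.86.

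**Type I error.** Under the stated assumptions totals and differences are independent, so passing the pre-test does not disturb the t-test: its simulated error given a pass is about 5% at every ρ. Only if a rejection were followed by a first-period-only comparison would overall error rise, to about 7–8%, because the first-period contrast is correlated with the totals.

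**Washout.** 14 × 24 h = 336 h; 336/14 = 24 half-lives and 336/10 = 33.6.

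**The case against.** The best reply is that the test is not the plan's main protection. The section rests first on washout, and 24–34 half-lives is strong support for no direct drug carryover. The carryovers of half or all of the treatment effect used above are therefore stress tests, not expected values, and the document gives no mechanism that would produce them. A carryover in the same direction as the benefit would also shrink the estimate, so it would not create a false claim of benefit. All of this stands. It also means that, if the washout does its work, nearly every rejection would be a false alarm, which is a reason to drop the condition.

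Three stronger readings are tempting, and the document does not support them.

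- A reader might infer that the two-stage rule inflates type I error. That needs a first-period-only fallback, which the article does not state; the rule as written leaves the t-test at about 5%.
- A reader might infer that a chance rejection leaves no valid primary analysis. With no true carryover the t-test on period differences stays valid; the article merely does not say what is done. A fallback may stand in a full protocol or analysis plan that is not shown, so its absence here carries little weight.
- A reader might infer that the no-carryover assumption has no support at all. It has the washout; what lacks support is the role given to the test.

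It is also fair to say that the variable, level and correlation are my assumptions. Over the ranges shown, detection of a full-size carryover stays at or below about one in three.

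**Conclusion.** The concern holds in a limited form. The article fixes a rule under which the treatment t-test follows a preliminary test that is credited with ruling out carryover, and a test of this kind in about 23 completers cannot do that. A carryover equal to the planned effect would halve the estimate and reduce power to about 37%, and would be caught about 7–20% of the time at the 5% level or about 14–31% at 10%. Without carryover the cost is a needless rejection about 4–5% of the time per primary endpoint and, if the analysis were abandoned, about 4 points of power.

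These figures rest on a test of patient totals, normal errors, 12 and 11 completers, the plan's 90% power and an assumed correlation of 0.3–0.8. The rule should be changed. It does not invalidate the trial, because the washout and the within-patient comparison are sound without it.

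**What to change.** In Data management and analysis, delete the preliminary test as a precondition, together with the clause that makes the t-tests wait for its result. State that the two-sample t-test on period differences, or the equivalent mixed model, will be run regardless. Give the 14-day washout (24–34 half-lives) as the ground for assuming no carryover.

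As a sensitivity analysis that nothing depends on, repeat the comparison with the last exercise test of each period, Week 3 against Week 6. In liraglutide-first patients the Week 6 test falls about three weeks after the crossover instead of two.

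Any carryover contrast should be reported descriptively, with an interval, and not offered as proof of absence. This includes a comparison of Week 5 to Week 6 change in one sequence with Week 2 to Week 3 change in the other. That is again a contrast of about 12 against 11 patients, and it is confounded with period and repeat-test effects.

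The cost is a few sentences. Table 7 already schedules the exercise tests, so no new data or visits are needed.

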**Table 5 Tab5:** **Exclusion criteria**

•	An abnormal resting electrocardiogram including atrial fibrillation, bundle brunch aberration or other conduction disturbance
•	Pre-existing significant left ventricular systolic dysfunction (ejection fraction <40%)
•	Pre-existing ischaemic or non-ischaemic cardiomyopathy
•	Pre-existing haemodynamically significant valvular heart disease
•	Inability to safely negotiate an exercise treadmill
•	Patients with Type 1 diabetes mellitus
•	Patients with Type 2 diabetes mellitus taking oral and/or subcutaneous anti-diabetic therapy
•	Patients with a personal or family history of medullary thyroid carcinoma
•	Patients with Multiple Endocrine Neoplasia syndrome type 2
•	Patients with acute renal failure or deteriorating renal function

Both investigator and patient will be blinded to the study drug. Patients will be randomised to enter a GLP-1 treatment arm or matched-volume saline placebo arm. Following a 1-week run-in phase with 0.6 mg liraglutide followed by a 1-week course of 1.2 mg liraglutide, patients in the active intervention arm will have their first exercise tolerance test (ETT) at the end of Week 2. Patients will then be up-titrated to high-dose 1.8 mg liraglutide for another week before performing a Week 3 ETT. With a stepwise increase in liraglutide therapy over a 3-week period we hope to observe a dose–response effect on exercise haemodynamics. An initial 1-week run-in phase of once daily 0.6 mg liraglutide should also allow for improved gastrointestinal tolerability. Whilst in the placebo arm, patients will have matched-volume saline injections for the first two weeks before the Week 2 ETT and then another week of saline injections before the Week 3 ETT. Patients will then crossover at this stage so that those in the treatment arm cross to the placebo arm and vice versa (please refer to Figure 1).

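### If all four exercise tests enter the least-squares regression, it has no patient-by-period error term, and its active-versus-placebo standard error is too small whenever such variation exists

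*Protocol article*

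**What the plan says.** The Data management and analysis section of the protocol article names two analyses of treatment. The first is "standard two-sample t-tests for independent samples using the intra-individual differences between the outcomes in both study periods as the raw data". The second follows in the next paragraph: "A multiple regression model will be used to compare treatment, visit number, and patient, using least squares". One significance threshold, p<0.05, is stated for the section as a whole. The article does not say which analysis decides the primary outcomes.

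The Study design text after Table 5 places the active-arm "first exercise tolerance test (ETT) at the end of Week 2", following the 1.2 mg week. Patients are then "up-titrated to high-dose 1.8 mg liraglutide for another week before performing a Week 3 ETT". The placebo arm has its Week 2 test and "then another week of saline injections before the Week 3 ETT". Patients then cross over. Table 7 lists ETTs at Weeks 2, 3, 5 and 6, so each patient has four tests, two in each period.

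**The concern.** Treatment is assigned to a whole period. A patient therefore supplies one active-versus-placebo contrast, however many ETTs are done within each period. The error for that contrast must include whatever makes one of a patient's periods differ from the other beyond the common period and treatment effects. A least-squares model with only treatment, visit and patient terms has one residual. It pools test-to-test variation within a period with variation between periods, and uses the pool to judge treatment.

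The patient term removes a constant level for each patient. It does not remove a patient-specific response to liraglutide or a shift that affects both tests of one period. In a two-period crossover, patient-by-treatment and patient-by-period variation cannot be told apart within a sequence, so any heterogeneity of response enters here.

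At stake is a regression p-value and interval that look firmer than the design allows. They could show significance where the period-difference t-test does not, with nothing in the article to say which counts.

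**Working it through.** **Inputs.** 26 patients randomised 1:1 (Sample size calculation); four ETTs each, at Weeks 2, 3, 5 and 6 (Table 7); treatment switched once, after Week 3 (Study design). The article prints no figure for this model and no within-period correlation. The share ρ below is therefore an assumption: ρ = patient-by-period variance ÷ (patient-by-period variance + test-to-test variance).

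**Degrees of freedom, all four ETTs, treatment coded active or placebo.**
- Observations: 26 × 4 = 104.
- Residual: 104 − 26 (patients) − 3 (visits) − 1 (treatment) = 74.
- Of these, patient-by-period: 26 − 1 (period) − 1 (treatment) = 24.
- Within period: 26 × 2 − 2 (visit within period) = 50. Check: 24 + 50 = 74.

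With 24 patients the same count gives 96 − 24 − 3 − 1 = 68, of which 22 are patient-by-period.

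**Standard error.** Let g = ρ/(1 − ρ), in units of the test-to-test variance. The variance that belongs to the treatment contrast is proportional to 1 + 2g. The pooled residual estimates (24(1 + 2g) + 50)/74 = 1 + 2g × 24/74. Hence model SE ÷ true SE = √[(1 + 2g × 24/74)/(1 + 2g)].

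- ρ = 0: g = 0, ratio 1.00.
- ρ = 0.1: g = 0.111, √(1.072/1.222) = 0.94.
- ρ = 0.3: g = 0.429, √(1.278/1.857) = 0.83.
- ρ = 0.5: g = 1, √(1.649/3) = 0.74.

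**Type I error** at nominal 5%, from 20,000 simulated null trials per setting:

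| ρ | Least squares, 26 patients | Least squares, 24 patients | t-test on period means, 26 patients |
|---|---|---|---|
| 0 | 4.9% | 4.9% | 5.0% |
| 0.1 | 6.8% | 6.7% | 5.1% |
| 0.3 | 10.6% | 10.2% | 5.1% |
| 0.5 | 14.6% | 14.5% | 5.0% |

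A different assumed structure, correlation decaying by calendar week at 0.2, 0.4, 0.6 or 0.8 per week, gives true SE ÷ model SE of 1.13, 1.24, 1.33 and 1.41. Type I error is then 8.0%, 11.4%, 14.2% and 16.7% (26 patients).

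**If treatment is coded by dose** (placebo, 1.2 mg, 1.8 mg). There is one more parameter, so 73 residual degrees of freedom, and the pooled residual is 1 + 2g × 24/73. The true variance is proportional to 1 + g for each dose against placebo, to 1 + 2g for the average of the two doses against placebo, and to 1 for 1.8 against 1.2 mg. Model SE ÷ true SE:

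| ρ | Each dose vs placebo | Average of doses vs placebo | 1.8 vs 1.2 mg |
|---|---|---|---|
| 0.1 | 0.98 | 0.94 | 1.04 |
| 0.3 | 0.95 | 0.83 | 1.13 |
| 0.5 | 0.91 | 0.74 | 1.29 |

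**If only one ETT per period enters.** The residual is 52 − 26 − 1 − 1 = 24 degrees of freedom, and the fit is algebraically the two-sample t-test on period differences. The problem does not arise.

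**The case against.** The strongest reply is that the model is one sentence in a journal article. It does not say that all four ETTs enter, how treatment is coded, or what role the regression has. The patient term already absorbs constant within-patient correlation, so at ρ = 0 the standard error is exactly right. A valid treatment test is also set out first in the same section.

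Much of this stands. A reader might infer that the regression's standard error is too small as a matter of fact. The documents do not support that, because they give no patient-by-period variance and the size of the error depends on it. A reader might also infer that the two ETTs in a period are being treated as replicates. The label does not fit: in the active period they follow different doses, and visit is in the model. Nor does the point show that the trial's treatment test is invalid, since the t-test is sound in this respect.

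What remains is that a visit term alongside patient points to all four tests, and the stated method has no term for the level at which treatment is applied. Coding by dose reduces the error for single-dose contrasts but does not supply that term. Zero patient-by-period variation would require, among other things, that all patients respond alike. That sits awkwardly with the plan to relate outcome parameters to baseline characteristics. It also sits awkwardly with the Concomitant medication section, under which antihypertensive treatment may be changed after the withdrawal of other drugs. These make a share above zero plausible; they do not say how large it is.

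**Conclusion.** The point holds conditionally and is confined to the regression. If all four ETTs enter, the model as stated tests treatment on 74 residual degrees of freedom where the crossover has 24, and it is anti-conservative for active versus placebo whenever there is any patient-by-period variation. Over an assumed share of 0.1 to 0.5, the standard error is about 6% to 26% too small and type I error runs from about 7% to between 14% and 15%. With dose coding, each dose-versus-placebo standard error is about 2% to 9% too small, while the comparison of the two doses errs in the conservative direction.

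The t-test on period differences keeps its nominal level if each patient contributes one difference per outcome. The matter is worth correcting because the remedy is cheap and the article does not rank the two analyses. It is not a flaw in the crossover comparison itself.

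**What to change.** Fit the regression as a linear mixed model with fixed effects for treatment, visit (or period and test within period) and a treatment-by-test term, random effects for patient and patient-by-period, and Kenward-Roger degrees of freedom. The treatment-by-test term carries the dose comparison and is needed to keep the dose–response aim in the Study design section. Collapsing to one value per period would also remove the error problem, but averaging the two tests would lose that comparison.

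State that the period-difference t-test, with one difference per patient, decides the primary outcomes and that the regression is supportive.

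The cost is one sentence of text, standard software and no new data. Active-versus-placebo intervals from the regression become wider: over the assumed shares of 0.1, 0.3 and 0.5 the correct standard error is about 1.07, 1.21 and 1.35 times the least-squares one. The interval for 1.8 versus 1.2 mg would become narrower.
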